
### Handling of missing data

2.10

Missing data will be traced and verified, and if they cannot be retrieved, they will be marked as missing in the database. Participants with missing data on the exposure or the primary outcome will not be imputed and will be excluded from the analysis. The proportion and pattern of missing data will be summarized for all variables, including baseline characteristics, covariates, and secondary outcomes.

The missing-data mechanism will be assessed using Little's missing completely at random (MCAR) test. When the data are compatible with MCAR and the variable-specific missingness is below 5%, missing values will be imputed using the k-nearest neighbors (KNN) algorithm. Otherwise, missing values in the minimal adjustment set identified by the DAG and in secondary outcomes will be assumed to be missing at random (MAR) and handled using multiple imputation. The imputation model will include the exposure variable, primary outcome, secondary outcomes, the minimal adjustment set identified by the DAG, and relevant auxiliary variables when available. Multiple imputation will be performed using 20 imputed datasets with a maximum of 50 iterations. Predictive mean matching will be used for continuous variables, while logistic regression will be used for categorical variables. Estimates from the imputed datasets will be combined using Rubin's rules.

As a sensitivity analysis, the primary analysis will be repeated using complete-case data and compared with the results based on multiple imputation. If substantial differences are observed between the two approaches, the potential influence of missing not at random (MNAR) mechanisms on the study findings will be discussed.

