**Methods:**

This single-center, prospective cohort study will enroll 346 adult patients undergoing elective cardiac surgery with CPB. Arterial blood samples will be obtained at multiple intraoperative time points to calculate TWA lactate. Patients will be classified into exposure and non-exposure groups based on a TWA lactate cutoff of ≥2.0 mmol/L. The primary outcome is the incidence of infection within 30 days of surgery. A predefined directed acyclic graph will guide covariate adjustment. Multivariable logistic regression will estimate the risk association, and restricted cubic spline models will explore potential nonlinear relationships. Sensitivity analyses will use lactate load, defined as the area under the lactate–time curve during CPB, to examine whether cumulative intraoperative lactate exposure yields results consistent with those obtained using TWA.

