### Sample size calculation

2.3

Previous studies have reported that the incidence of postoperative infection after cardiovascular surgery is approximately 10.4%–15.5% (21–23). To obtain a conservative sample size estimate and avoid overestimating the expected event rate, we used the lowest reported incidence of 10.4% as the baseline infection rate in the normal lactate group. The same study that reported this baseline incidence also reported an odds ratio (OR) of 2.75 for postoperative infection in the high-lactate group compared with the normal-lactate group (21). With a two-sided *α* of 0.05 and a power of 0.9, the required sample size per group was estimated to be 156 using PASS 2021 software (NCSS, LLC, Kaysville, UT, USA), resulting in a total sample size of 312. Considering a 10% loss to follow-up, at least 173 participants per group are needed, for a total of 346 participants.

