### Statistical analysis

2.9

Data with a normal distribution will be expressed as mean ± standard deviation (SD), non-normally distributed data as median and interquartile range (IQR), and categorical variables as frequency (n) and percentage (%). Baseline data will be compared using two-sample t-tests, Mann–Whitney U tests, or chi-square tests. Univariate logistic regression analysis will be used to evaluate the association between TWA lactate, covariates, and postoperative infection, calculating odds ratios and 95% confidence intervals (95% CI). The following are the primary analyses: according to the DAG (Figure 4), confounders that are common causes of both TWA lactate and postoperative infection will be adjusted for, whereas mediators and colliders on the causal pathway will not be adjusted. In the model, TWA lactate will be analyzed as both a categorical variable and a continuous variable. Multivariable logistic regression will be employed to assess the risk association between TWA lactate and postoperative infection, reporting adjusted odds ratios (aOR) and 95% CI. For the continuous analysis, aOR will be reported per 0.5 mmol/L increase, per 1.0 mmol/L increase, and per 1-standard deviation increase in TWA lactate. For the categorical analysis, TWA lactate will be dichotomized according to the prespecified cutoff of 2.0 mmol/L. The median of tertiles will be used as a quasi-continuous variable to analyze the linear trend between TWA lactate and postoperative infection risk. Restricted cubic spline regression will be applied to explore the potential nonlinear relationship between TWA lactate and postoperative infection. Threshold analysis will be performed using segmented regression, and the likelihood ratio test will be applied to compare the goodness-of-fit between linear and nonlinear models to identify the optimal model. Based on the determined threshold, an adjusted segmented linear regression model will be constructed to estimate aOR and 95% CI before and after the threshold. The following are the secondary analyses: prespecified subgroup analyses will be conducted according to key characteristics, including age, sex, preoperative comorbidities, and surgery type, and interaction effects will be evaluated. To assess robustness, we will perform sensitivity analyses using lactate load and peak lactate during CPB, and repeat the statistical analyses. To control the error of type I due to multiple comparisons, *P* values for secondary outcomes and prespecified subgroup interaction tests will be adjusted using the Holm–Bonferroni method. All statistical tests are two-sided, and *P* < 0.05 is considered statistically significant.

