#### Data collection

2.11.1

All enrolled participants will have their Case Report Forms (CRF) completed by trained research personnel. Data collection will follow a dual-track system, using both paper CRFs and electronic data entry, with subsequent cross-checking for consistency. Face-to-face follow-ups will be conducted for patients who remain hospitalized, while telephone follow-ups will be used for those who have been discharged.

Demographics and baseline characteristics: age (years), sex (male/female), BMI (kg/m^2^), smoking history (yes/no), alcohol consumption (yes/no), and NYHA functional classification (I–IV).

Preoperative comorbidities: hypertension (yes/no), diabetes (yes/no), arrhythmia (yes/no), history of cerebrovascular disease (yes/no), pulmonary comorbidities (yes/no), obesity (yes/no), anemia (yes/no).

Preoperative laboratory and functional indices: preoperative lactate (mmol/L), preoperative blood glucose (mmol/L), hemoglobin (g/L), platelet count (10⁹/L), hypoproteinemia (yes/no), serum total protein (g/L), serum albumin (g/L), lymphocyte count (10⁹/L), monocyte count (10⁹/L), neutrophil count (10⁹/L), TBIL (μmol/L), creatinine (μmol/L), BNP (pg/mL), CRP (mg/L), LvEF (%), cardiac troponin I (CTnI, μg/L), myoglobin (Mb, μg/L), ALT (U/L), AST (U/L), and BUN (mmol/L).

Surgery-related variables: type of surgery (coronary artery bypass grafting, valve surgery, major vascular surgery, cardiac tumor resection, combined surgery, other), surgical time (min), CPB time (min), aortic cross-clamp time (min), intraoperative temperature ( °C), lactate level at the end of CPB (mmol/L), body temperature before surgery, during CPB, and at the end of surgery ( °C); duration of body temperature below 32 °C during CPB (min).

Intraoperative physiological and anesthesia-related parameters: anesthesia duration (min), blood gas indices including lactate (mmol/L), pH, hematocrit (%), blood glucose (mmol/L) and NEE from the end of CPB to the end of surgery (µg/kg).

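### The planned missing-data sensitivity analysis cannot respond to loss of the primary outcome, because both analyses it compares leave out the same patients

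*Protocol article*

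**What the plan says.** The primary outcome is cumulative and binary: "The primary outcome is the incidence of infection within 30 days of surgery" (Abstract, Methods). The primary model has no censoring: "Multivariable logistic regression will be employed to assess the risk association between TWA lactate and postoperative infection" (section 2.9).

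On missing data, section 2.10 fixes three things:

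- For exposure and primary outcome: "Participants with missing data on the exposure or the primary outcome will not be imputed and will be excluded from the analysis".
- Imputation is for the other variables. Multiple imputation covers the DAG adjustment set and the secondary outcomes, with k-nearest neighbours used when missingness is low and compatible with MCAR.
- The sensitivity analysis is that "the primary analysis will be repeated using complete-case data and compared with the results based on multiple imputation". MNAR is then a matter for discussion, and only when the results of the two differ substantially.

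Loss is expected. The sample size in section 2.3 is inflated with the words "Considering a 10% loss to follow-up", and under section 2.11.1 "telephone follow-ups will be used for those who have been discharged". Table 1 schedules infection assessment on postoperative days 1, 2, 3, 7, 14 and 30. The other sensitivity analyses, in section 2.9, change only the lactate metric (load and peak).

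**The concern.** A complete-case set is by construction a subset of the patients with an observed outcome. The multiple-imputation analysis uses all patients with an observed outcome, and the complete-case analysis uses those of them who also have complete covariates. Neither contains a patient whose outcome is missing, so the two can differ only through covariate handling. The plan nevertheless makes any consideration of MNAR depend on their differing. Outcome loss, the form of missingness that the sample size allows for, cannot set off that trigger.

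The outcome definition adds an asymmetry. An infection seen on day 5 already answers whether infection occurred within 30 days. A patient discharged well who cannot be reached on day 14 or 30 has an unknown answer. On that reading, exclusion falls on patients who were infection-free at last contact and discards the infection-free days already observed. At stake are the reported 30-day incidence and, if loss differs between the lactate groups, the adjusted odds ratio.

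**Working it through.** **Inputs from section 2.3.** Risk 10.4% with normal lactate, OR 2.75, two-sided alpha 0.05, power 0.90, 156 per group, 10% loss, 173 per group. The upper end of the cited incidence range is 15.5%.

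**The plan's own figure.** Odds in the high-lactate group: 2.75 × 0.104/0.896 = 0.319, so the risk is 0.319/1.319 = 24.2%. The pooled two-proportion formula gives 156 per group (power 0.9003), as stated. 156/0.9 = 173.3, against the stated 173. The sample size is not at issue here.

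**Incidence.** If 10% of the cohort is excluded, all are non-cases and none is infected later, the analysed incidence is p/0.9:

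- 0.104/0.9 = 11.6%
- 0.155/0.9 = 17.2%

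This is the ceiling. Later infections among the lost make the inflation smaller.

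**Odds ratio.** Let l be the share of a group lost, and g the share of infections in lost patients that are seen before loss. Analysed cases are proportional to p[(1 − l) + l·g] and analysed non-cases to (1 − p)(1 − l). The group's odds are therefore multiplied by [(1 − l) + l·g]/(1 − l), and the OR by the ratio of these factors, exposed over unexposed. The documents give neither l by group nor g, so the values below are assumptions.

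| Loss, unexposed / exposed | g = 0 | g = 0.7 | g = 1 |
|---|---|---|---|
| 10% / 10% | 2.75 | 2.75 | 2.75 |
| 5% / 15% | 2.75 | 2.98 | 2.75 × 0.95/0.85 = 3.07 |
| 15% / 5% | 2.75 | 2.54 | 2.75 × 0.85/0.95 = 2.46 |

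With equal loss and g = 0.7 the analysed risks rise to 11.1% and 25.6%, but the OR does not move.

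**Would the planned comparison notice?** A simulated cohort of 800,000 had one covariate related to both exposure and infection, 10% of that covariate missing at random draw, and g = 0.7. The imputation analysis was given its best case, with the covariate fully known.

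| Loss, unexposed / exposed | No loss (truth) | Ideal covariate imputation | Complete case |
|---|---|---|---|
| 10% / 10% | 2.754 | 2.752 | 2.744 |
| 5% / 15% | 2.754 | 2.985 | 2.991 |
| 15% / 5% | 2.754 | 2.543 | 2.533 |

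In the last two rows the two planned analyses agree with each other and both miss the truth, so the MNAR condition would not be met.

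**Bounds at the planned size.** Take 156 analysed and 17 lost per group. Expected events are 156 × 0.104 = 16.2 and 156 × 0.242 = 37.7.

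- All lost uninfected: (37.7/135.3)/(16.2/156.8) = 2.70
- All lost infected: (54.7/118.3)/(33.2/139.8) = 1.95
- Only the lost exposed infected: (54.7/118.3)/(16.2/156.8) = 4.47
- Only the lost unexposed infected: (37.7/135.3)/(33.2/139.8) = 1.17

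The planned comparison would show none of this range.

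**The case against.** The best defence has four parts.

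- **The asymmetry is inferred.** The article does not say when a partly followed patient counts as having a missing outcome. That detail may sit in a fuller document. This stands: that only infection-free patients are removed follows from the outcome definition, not from any stated rule.
- **There are safeguards.** Section 2.10 has missing data traced first and has the amount and pattern of missingness summarised for all variables, so outcome loss would be visible. It nowhere claims that agreement between the two analyses vindicates the exclusion. This also stands, but a count of lost patients does not show what their loss does to the estimate.
- **The main estimate is an association.** Equal loss leaves the OR unchanged. Bias needs a difference in loss that remains after adjustment for the DAG set. The assumed shifts are modest beside sampling error: at the planned counts the standard error of the unadjusted log OR is √(1/16.2 + 1/139.8 + 1/37.7 + 1/118.3) = 0.32, which gives a 95% interval of about 1.46 to 5.17 around 2.75. The extreme shift, ln(0.95/0.85) = 0.11, is about a third of that standard error. This limits the severity.
- **A censored time-to-infection analysis is no clear remedy.** It assumes non-informative censoring, and sections 2.11.1 and 2.9 list no infection-onset date. This stands, and such an analysis is not asked for here.

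A reader might infer that the odds ratio is probably biased because early discharge drives loss. The documents give no loss rates by lactate group and nothing that ties loss to discharge day. Neither the presence nor the direction of bias can be asserted.

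**Conclusion.** The point holds in a limited form. It is certain, without any assumption about loss, that the multiple-imputation versus complete-case comparison omits every patient with a missing primary outcome on both sides, so it cannot inform on outcome loss, and that the MNAR condition is tied to the wrong signal.

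The size of any harm is conditional. If infection recorded before loss settles the outcome, the 30-day incidence is inflated, at most from 10.4% to 11.6% at 10% loss with no later infections. The OR moves only if loss differs by lactate group after adjustment, to between 2.46 and 3.07 in the assumed 5% versus 15% extremes. The 10% is a planning allowance, not a forecast. The documents do not support the stronger conclusion that the plan's rule demonstrably biases the primary odds ratio. This should be corrected before data lock, but it does not undermine the design.

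**What to change.** Keep the primary logistic model. Add to section 2.10 a prespecified sensitivity analysis for missing outcomes that retains every patient with a valid exposure and

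- counts any infection recorded before loss as an event;
- multiply imputes unknown post-discharge infection status from exposure, the adjustment covariates and the last infection-free visit;
- reports bounds that set lost patients to infected or uninfected, separately by lactate group.

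Keep the complete-case comparison, but label it as a check on covariate missingness. Remove the condition that MNAR is considered only if the two analyses differ. A time-to-first-infection analysis is optional.

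The cost is a few sentences and a few extra model runs, with no added patients or visits. The last infection-free visit comes from the infection assessments already scheduled in Table 1. The downside is that the reported range may be wider.

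### The KNN branch for variables under 5% missing has no variance pooling and gains nothing over the multiple imputation already planned; the effect is minor and falls mainly on secondary outcomes

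*Protocol article*

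**What the plan says.** All of this is in section 2.10 of the protocol article.

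- **Exposure and primary outcome:** "Participants with missing data on the exposure or the primary outcome will not be imputed and will be excluded from the analysis".
- **The gate:** "The missing-data mechanism will be assessed using Little's missing completely at random (MCAR) test".
- **KNN branch:** two conditions must hold together, "When the data are compatible with MCAR and the variable-specific missingness is below 5" per cent; then "missing values will be imputed using the k-nearest neighbors (KNN) algorithm".
- **Other branch:** missing values in the DAG adjustment set and in secondary outcomes "will be assumed to be missing at random (MAR) and handled using multiple imputation". The settings follow: "Multiple imputation will be performed using 20 imputed datasets with a maximum of 50 iterations", and "Estimates from the imputed datasets will be combined using Rubin's rules".
- **Sensitivity analysis:** "the primary analysis will be repeated using complete-case data and compared with the results based on multiple imputation". A substantial difference between the two leads to a discussion of MNAR.

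The KNN sentence is not limited to covariates, and nothing exempts secondary outcomes from it. Section 2.9 puts the P values of the secondary outcomes through Holm–Bonferroni.

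**The concern.** The multiple datasets and Rubin's rules are attached to multiple imputation only. As written, KNN fills each gap with one value, and the model treats that value as measured. The uncertainty about it is lost, so standard errors come out too small.

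The gate does not justify the switch. Failure to reject in Little's test is not evidence for MCAR, and the test has least power when little is missing, which is when this branch applies. Even if MCAR held, multiple imputation would still be valid. If MCAR failed but MAR held, multiple imputation would be the safer method. In neither case does KNN offer an advantage.

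At stake are the confidence intervals for imputed covariates, the P values of imputed secondary outcomes that enter the Holm procedure (which needs valid P values as input), and the coherence of the sensitivity comparison.

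**Working it through.** **1. The plan's own figure.** Section 2.10 gives no figure for standard errors. The design in section 2.3 was reproduced first, because it sets the scale for the simulation.

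- Inputs: 10.4% infection in the normal-lactate group, OR 2.75, two-sided alpha 0.05, power 0.90.
- Odds in the high-lactate group = 2.75 × 0.104/0.896 = 0.319, so p2 = 0.319/1.319 = 0.242.
- n per group = [1.96·√(2·p̄·(1−p̄)) + 1.2816·√(p1(1−p1) + p2(1−p2))]² / (p2−p1)², with p̄ = 0.173.
- This is (1.048 + 0.674)² / 0.138² ≈ 156 per group, 312 in total, as stated.

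**2. Effect on the primary odds ratio.** Logistic regression was simulated with n = 312 and OR 2.75. Every covariate was 4.9% missing under MCAR; exposure and outcome were complete, as section 2.10 implies for the analysed patients. Assumptions not in the documents: 5 or 10 normal covariates with correlation 0.3, half the patients exposed, k = 5 neighbours, multiple imputation by a normal model rather than predictive mean matching, 300 and 200 replicates.

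| Quantity | 5 covariates | 10 covariates |
|---|---|---|
| Mean SE of exposure log-OR, KNN | 0.359 | 0.364 |
| Mean SE of exposure log-OR, multiple imputation | 0.360 | 0.366 |
| SE ratio KNN/MI, exposure | 0.997 | 0.995 |
| SE ratio KNN/MI, an imputed covariate's coefficient | 0.986 | 0.983 |
| Exposure SE / empirical SD, KNN | 1.046 | 0.926 |
| Exposure SE / empirical SD, multiple imputation | 1.042 | 0.931 |
| Exposure SE / empirical SD, full data | 1.038 | 0.934 |
| Mean SE of exposure log-OR, complete case | 0.411 | 0.488 |

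The exposure SE is 0.3% to 0.5% smaller under KNN, and the covariate SE 1.4% to 1.7% smaller. Against the empirical SD, KNN and multiple imputation are equally calibrated. The empirical SDs carry Monte Carlo error of about 1/√(2×299) = 4.1% and 1/√(2×199) = 5.0%, so the departures of those ratios from 1 mean little. The KNN/MI ratios compare the same simulated datasets and are steadier.

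**3. Effect on an imputed secondary outcome.** Take the mean of a continuous outcome with a fraction m filled by its predicted value, where the prediction explains a share R² of the variance.

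- Naive variance factor: (1−m) + m·R².
- Correct variance factor: (1−R²)/(1−m) + R².
- SE ratio = √(naive/correct).
- m = 0.05, R² = 0: √(0.95/1.0526) = 0.950.
- m = 0.05, R² = 0.3 (assumed): √(0.965/1.0368) = 0.965.
- m = 0.01, R² = 0: 0.990.

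The SE is therefore 3.5% to 5% too small at the limit and 1% or less at 1% missing. At ratio 0.95, the true error of a nominal 5% test is 2·[1 − Φ(1.96 × 0.95)] = 2·[1 − Φ(1.862)] = 6.3%.

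**4. The sensitivity comparison.** If Little's test does not reject and every incomplete variable is under 5% missing, the rule sends all of them to KNN. The complete-case analysis is still run, but the result named as its comparator does not exist.

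**The case against.** The best defence is that the rule limits its own harm. Exposure and primary outcome are excluded rather than imputed, KNN needs both conditions, and anything at 5% or more goes to multiple imputation. The text also never says that KNN is done once; that is inferred from Rubin's rules being attached to the other method. The limits on harm stand and decide the size of the point. The inference is fair, since no pooling is given for KNN and it is set up as the alternative to multiple imputation.

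Four stronger readings are tempting and are not supported:

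- **That the primary confidence interval is materially too narrow.** KNN reaches the primary aOR only through covariates, and the SE changes by at most about 0.5% in the simulation. The 5% and 6.3% figures belong to secondary outcomes near the limit.
- **That KNN is worse than complete-case analysis because the latter is unbiased under MCAR.** Complete-case analysis discards patients. With 10 covariates at 4.9% missing, 1 − 0.951^10 = 39% would be dropped, and its exposure SE was 0.488 against 0.364 for KNN.
- **That the per-variable limit allows great harm because many patients could carry a filled value.** That 39% also needs independent missingness at the limit in every variable, and the documents give no such rates. Even there the exposure SE ratio was 0.995.
- **That the KNN branch has no sensitivity analysis.** Section 2.10 commits to the complete-case repeat without restricting it to a branch. Only the stated comparator is lacking.

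**Conclusion.** The point holds, and it is minor. The plan states a weaker method where it already contains a better one, and the test that selects the weaker method cannot justify the choice. The primary aOR is practically unaffected under the simulation's assumptions. The understatement of the SE is about 1.5% for an imputed covariate's own coefficient, and 3.5% to 5% for a secondary outcome that is 5% missing with R² of the imputation between 0 and 0.3; it shrinks as missingness falls. The gap in the sensitivity comparison does not depend on these sizes, but arises only if KNN is used throughout. The sample size is unaffected. This is an improvement that costs nothing, not a threat to the study's main conclusion.

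**What to change.** In section 2.10, delete the Little's-test gate and the KNN branch. Use the multiple imputation already specified (20 datasets, Rubin's rules, with exposure and outcomes in the imputation model) for the adjustment set and the secondary outcomes at any percentage missing. Keep the exclusion of patients with missing exposure or primary outcome as it stands. Keep complete-case analysis as the sensitivity analysis, which then always has its comparator. Little's test may still be reported descriptively.

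The cost is wording only: the multiple-imputation procedure is already part of the plan, and neither data collection nor sample size changes.
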